### Recruitment

Participants will be recruited in the general population by means of a Facebook advertisement campaign, messages on panic or anxiety related online forums, banners on health related websites and advertisements in newspapers. Interested individuals will be directed to a study website, where they can find further information as well as an informed consent form. They can apply for participation by printing and signing the informed consent form, which can be scanned and sent by e-mail or sent by postal mail. After application, the researchers will send the participants a link to an online questionnaire.

### Randomisation and procedure

After screening and completion of the baseline questionnaires (t0), the participant will be contacted for a diagnostic interview by telephone. The interview will be conducted within two weeks after baseline by a trained and experienced interviewer. All participants will be randomised to one of the two groups, regardless of the presence or absence of a diagnosis. Randomisation will be stratified for the presence or absence of agoraphobia symptoms (PDSS-SR item 4 score > 1) and the use of medication. Randomisation lists are generated with a computer program. Blinding of the participants and researchers is not possible due to the design of this research. The post-treatment assessment (t1) is scheduled at 3 months after baseline. Both the baseline and the post-treatment assessments are self-report and will be conducted through the Internet.

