**Methods:**

Participants with mild or sub-clinical PD (N = 128) will be recruited in the general population. Severity of panic and anxiety symptoms are the primary outcome measures. Secondary outcomes include depressive symptoms, quality of life, loss of production and health care consumption. Assessments will take place on the Internet at baseline and three months after baseline.

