## Methods

### Design

We will conduct a randomised controlled trial with two arms: (a) Internet based self-help with minimal guidance, (b) waiting list control group with information website. The Medical and Ethical Committee of VU Medical Centre approved the study protocol.

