### Intervention

Don't Panic Online (DPO) is an individual guided web-based self-help course, based on cognitive behavioural therapy. It was developed by the Trimbos Institute, which is the Netherlands Institute for Mental health and Addiction, in collaboration with GGNet, a Dutch mental health care institute. The course consists of six sessions, in which the participants will learn to control their panic symptoms by applying various cognitive behavioural techniques and skills. The course's format is based on Colour Your Life, an evidence based Internet intervention for depressive symptoms [20,21].

DPO is a protocolised treatment and consists of the following components: keeping a log of panic attacks; analysis of fearful situations; challenging thoughts that enable feelings of panic; replacing these thoughts by more realistic, constructive thoughts that reduce anxiety; behavioural exercises; and ranking exercises from manageable to difficult and carrying them out in order of difficulty. Each session consists of text, voice over, animated diagrams and video. A typical session will take about thirty minutes and consists of an introduction, a discussion of the previous lesson's homework, new theory and homework for the next week. The course is designed to be followed on a weekly basis until session five, while the sixth lesson can be followed four weeks after the fifth. The course can be completed in eight weeks.

Besides the lessons, the participant has several online resources at his or her disposal: a homework station, a panic attack log, a library for extra information, reading tips and a discussion board.

The DPO website contains an e-mail system for contact between a participant and a coach. For the current study, the coach will reply to questions about the course, its exercises and the participant's mental health. He will also contact the user weekly to ask after his progress. Participants will be supported for a maximum of three months. The coaches will consist of students who are in the final phase of their study of clinical psychology. All will receive a brief training.

Participants in the control group will receive access to DPO after completing the t1 measurement. In the mean time, they will have access to an information website about PD.

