### Instruments

All variables will be measured at t0 and t1, except for demographic data, the diagnosis and satisfaction with the intervention. Demographic data and diagnosis are only measured at t0, while satisfaction with the intervention will only be measured at t1.

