#### Satisfaction and track-and-trace

A track-and-trace system will keep a record of the dates participants of the intervention group log on or finish a lesson. This system will also pose a question after each lesson: "Was this lesson useful to you?", which can be answered on a 5-point Likert scale. At t1, these participants will receive questions about their experience with the intervention. This includes the number of lessons followed, the amount of time spent on homework, satisfaction with the intervention and satisfaction with the coaching.

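### The statement that researchers cannot be blinded is too broad: nothing described prevents a primary analysis on coded arms (minor point)

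*Protocol article*

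**What the plan says.** Under Randomisation and procedure, the Protocol article disposes of blinding in one sentence: "Blinding of the participants and researchers is not possible due to the design of this research". It gives the design as the reason, groups participants and researchers together and makes no exception for any role.

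Other parts of the article describe that design:

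- **Comparator (Design):** "b) waiting list control group with information website".
- **Primary outcomes (Abstract, Methods):** "Severity of panic and anxiety symptoms are the primary outcome measures". Under Instruments these are the PDSS-SR and the BAI.
- **Mode of assessment (Randomisation and procedure):** "Both the baseline and the post-treatment assessments are self-report and will be conducted through the Internet".
- **Interview (Instruments):** "Demographic data and diagnosis are only measured at t0". The telephone CIDI is therefore not repeated at t1.
- **Coaching (Intervention):** "The coaches will consist of students who are in the final phase of their study of clinical psychology". Contact with participants runs through the e-mail system of the course website.
- **Data from the course arm only (Satisfaction and track-and-trace):** "A track-and-trace system will keep a record of the dates participants of the intervention group log on or finish a lesson", and "At t1, these participants will receive questions about their experience with the intervention".

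The article does not say who analyses the data, or whether that person sees the arm labels.

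**The concern.** The sentence claims an impossibility and rests it on the design. The claim is sound for anyone who receives, delivers or administers the course. It is not sound for the analysis, which can be done on a file that shows two arms without saying which had the course.

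What is at stake is limited. With no assessor at t1, the analyst can affect the result only through choices about data and model. The article leaves some of these open:

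- Sample size names regression imputation for missing values, while Analyses uses a linear mixed model to deal with them.
- Two measures, panic and anxiety severity, are called primary, while the power calculation covers the PDSS-SR alone.

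Methodological considerations also states a directional hypothesis in favour of the course. Settling such points without knowing which arm is which is a modest protection, and the sentence as worded appears to rule it out.

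**Working it through.** No figure is attached to the blinding statement, so the check is to ask, role by role, whether the described design makes masking impossible.

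1. **Participants.** One arm follows the course and the other waits with an information website. Participants know their arm, so masking is impossible and the sentence is right.
2. **Coaches.** They answer questions and contact course participants weekly (Intervention). Masking is impossible and the sentence is right.
3. **Staff who deal with participants.** Someone must give one arm access to the course, and the other arm access only after t1 (Intervention). Masking is impractical and the sentence is right.
4. **Interviewer.** Diagnosis is measured only at t0. The text describes the interview before randomisation, although that order is implied rather than stated. Either way, the interview yields no outcome at t1.
5. **Outcome assessor at t1.** There is none, because the assessments are online self-report.
6. **Analyst.** Analysing the PDSS-SR and BAI needs a participant number, scores at t0 and t1, an arm code and any covariates. None of these has to identify the arm. The fields that would do so are the log-in and lesson dates, the ratings after each lesson, and the t1 questions on experience, homework and coaching. All are collected from the course arm only, so their mere presence for a participant would break the code. They are not part of the PDSS-SR or BAI and can be kept in another file.

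The reason given therefore covers roles 1 to 3, is immaterial for 4 and 5, and does not cover 6.

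As a check that masking the analyst would leave the design figures alone, I reproduced the planned size. The inputs from Sample size are d = 0.50, two-sided alpha 0.05 and power 80%.

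- Normal approximation: n = 2 × (1.960 + 0.842)² / 0.50² = 2 × 7.85 / 0.25 = 62.8, that is 63 per group.
- Exact t calculation: 63.77, that is 64 per group, as stated.
- Power at 64 per group: 80.1%.

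Coding the arms enters none of these formulas, so N = 128, alpha and power stay as they are.

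**The case against.** The strongest reply is that the article never says the analyst is unmasked. Under Recruitment, researchers are the people who send participants the link to the questionnaire. Read that way, the blinding sentence means trial staff and is reasonable. Who analyses the data, and on what file, is commonly left to a full protocol or analysis plan, and neither is shown.

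Much of this stands. A reader might infer that the trial has knowingly accepted an avoidable bias, or that the analyst will know the allocation. The article supports neither, because it is silent on the analyst. What remains is that the sentence is more than silence. It asserts an impossibility for researchers without exception, and an analysis plan that masked the analyst would conflict with it unless the word is read narrowly.

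Two further objections also stand. Coding the arms does not touch the main bias, which is self-report by participants who know their arm. Nor does it settle the conflict between regression imputation and the mixed model; that needs one method chosen in advance. Analyses already fixes intention to treat, restricted maximum likelihood under missing at random, and the effect-size formula, so the analyst's room for choice is limited.

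**Conclusion.** The blanket statement is too broad and should be narrowed. The design explains why participants, coaches and participant-facing staff cannot be masked. It does not prevent an analysis of the PDSS-SR and BAI under coded arm labels.

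This is a minor point. The benefit is confined to choices made during analysis, and its size cannot be estimated from the article.

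A reader might infer from the power curve that small analytic shifts would decide the trial, since power is 80% at d = 0.50 but 71% at 0.45 and 61% at 0.40. That does not follow. Those figures are power at different true effects and do not describe shifts in an observed estimate. With 64 per arm and a simple t-test, the smallest significant observed d is about 1.979 × √(2/64) = 1.979 × 0.1768 = 0.35. Observed values of 0.50, 0.45 and 0.40 give t = 2.83, 2.55 and 2.26, with p about 0.005, 0.012 and 0.025, so all are significant. Only an estimate that happened to fall near 0.35 would be sensitive, and the article gives no reason to expect one.

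The conclusion assumes that the analysis can be done by, or on a file prepared by, someone other than the coaches and participant-facing staff. The article neither states nor excludes this.

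**What to change.** Replace the sentence under Randomisation and procedure with wording to this effect:

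*Participants, coaches and staff in contact with participants cannot be blinded. The primary analysis of the PDSS-SR and BAI will be carried out on a dataset in which the arms are coded A and B, and the code will be opened once that analysis is final. Log-in and lesson records, lesson ratings and the t1 questions on experience with the course will be kept in a separate file until then.*

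If a full protocol or analysis plan already provides for this, the sentence need only be brought into line with it.

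The cost is one revised sentence, a recoded data export and a short delay to the adherence and satisfaction analyses. Sample size, alpha, assessment schedule and conduct of the course do not change.

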### Intervention

Don't Panic Online (DPO) is an individual guided web-based self-help course, based on cognitive behavioural therapy. It was developed by the Trimbos Institute, which is the Netherlands Institute for Mental health and Addiction, in collaboration with GGNet, a Dutch mental health care institute. The course consists of six sessions, in which the participants will learn to control their panic symptoms by applying various cognitive behavioural techniques and skills. The course's format is based on Colour Your Life, an evidence based Internet intervention for depressive symptoms [20,21].

DPO is a protocolised treatment and consists of the following components: keeping a log of panic attacks; analysis of fearful situations; challenging thoughts that enable feelings of panic; replacing these thoughts by more realistic, constructive thoughts that reduce anxiety; behavioural exercises; and ranking exercises from manageable to difficult and carrying them out in order of difficulty. Each session consists of text, voice over, animated diagrams and video. A typical session will take about thirty minutes and consists of an introduction, a discussion of the previous lesson's homework, new theory and homework for the next week. The course is designed to be followed on a weekly basis until session five, while the sixth lesson can be followed four weeks after the fifth. The course can be completed in eight weeks.

Besides the lessons, the participant has several online resources at his or her disposal: a homework station, a panic attack log, a library for extra information, reading tips and a discussion board.

The DPO website contains an e-mail system for contact between a participant and a coach. For the current study, the coach will reply to questions about the course, its exercises and the participant's mental health. He will also contact the user weekly to ask after his progress. Participants will be supported for a maximum of three months. The coaches will consist of students who are in the final phase of their study of clinical psychology. All will receive a brief training.

Participants in the control group will receive access to DPO after completing the t1 measurement. In the mean time, they will have access to an information website about PD.

### Instruments

All variables will be measured at t0 and t1, except for demographic data, the diagnosis and satisfaction with the intervention. Demographic data and diagnosis are only measured at t0, while satisfaction with the intervention will only be measured at t1.

#### Demographic data

This section contains questions about age, gender and education.

#### Diagnosis

The Composite International Diagnostic Interview (CIDI) [22] will be used to ascertain the presence or absence of PD, other anxiety disorders and depression. The CIDI has been developed by the WHO and is an extensive, fully structured diagnostic interview to assess DSM-IV Axis-I diagnoses [22]. Only the subscales depression, PD, agoraphobia, GAD, social phobia and post-traumatic stress disorder will be used in this study. The reliability of these subscales is sufficient (inter-rater κ = .94 - .99; test-retest κ = .62 - .84) [23]. In this study, a trained interviewer will administer the CIDI by telephone.

#### Anxiety and panic symptoms

For severity of panic symptoms the Panic Disorder Severity Scale - Self Report (PDSS-SR) will be used. The PDSS is originally a face-to-face interview [24] and was adapted to self-report by Houck et al. [25]. The instrument contains seven items that assess the severity of seven dimensions of panic disorder and associated symptoms. The PDSS-SR generates a total score ranging from 0 to 28, with a higher score indicating more severe panic symptoms. The questionnaire has good psychometric properties with Cronbach's alpha = 0.92 and intraclass correlation coefficient = 0.81 [25]. In the current study, a score of 0-4 will count as no clinically relevant symptoms and 16 or higher as severe PD.

Anxiety symptoms in general will be measured with the Beck Anxiety Inventory (BAI) [26]. The BAI contains 21 short questions. Internal consistency is high, with Cronbach's alpha ranging from .90 to .94 [26]. The score varies from 0 to 63. A score of 30 or higher is interpreted as severe anxiety symptoms.

#### Depressive symptoms

Depressive symptoms we will be measured with the CES-D [27]. The CES-D is a 20-item self-report questionnaire. Every item ranges from 0 to 3 and the total score ranges from 0 (no feelings of depression) to 60 (severe feelings of depression). Radloff [27] reports high internal consistencies among different populations (.79 to .92). The optimal cut-off score varies between 16 and 27 [28]. In the current study, we will regard 27 and higher as a high score.

#### Suicidal risk

Suicidal risk and ideation will be measured with the specific section of the Mini-International Neuropsychiatric Interview (MINI) [29,30]. The MINI suicide section consists of 6 items and classifies subjects into four groups: no suicidal risk, low suicidal risk, moderate suicidal risk, and high suicidal risk. In this study, the items are self-report. Participants with moderate to high suicidal risk will be excluded from this study.

#### Quality of life

Quality of life will be measured with the Dutch version of the EuroQol Questionnaire (EQ-5D) [31,32]. This short list contains five dimensions: mobility, self-care, usual activities, pain/discomfort and anxiety/depression. The EQ-5 D generates a total of 243 unique health states, each of which is associated with a utility score ranging from 0 (poor health) to 1 (perfect health). The EQ-5 D is a validated instrument for measuring general health-related quality of life [31-33].

#### Loss of production and health care consumption

An indication of loss of production and use of care will be made with the Trimbos and Institute of Medical Technology Assessment Questionnaire on Costs Associated with Psychiatric Illness (TiC-P) [34]. This list consists of three parts. Part I measures health care consumption of individuals who suffer from mental disorders. Part II examines loss of production (indirect costs) and part III general, demographic variables. In the current study, part III will be omitted, because demographic variables are already measured elsewhere.

#### Satisfaction and track-and-trace

A track-and-trace system will keep a record of the dates participants of the intervention group log on or finish a lesson. This system will also pose a question after each lesson: "Was this lesson useful to you?", which can be answered on a 5-point Likert scale. At t1, these participants will receive questions about their experience with the intervention. This includes the number of lessons followed, the amount of time spent on homework, satisfaction with the intervention and satisfaction with the coaching.

### Analyses

Differences in demographic and baseline clinical characteristics will be computed with Chi-square tests, *t*-tests, and analysis of variance (ANOVA). The data of post-treatment measurements will be analysed in agreement with the intention to treat principle. Assuming missing data will be missing at random, the Linear Mixed Modeling (LMM) procedure will be used for all analyses to estimate missing values. LMM includes incomplete cases in the analysis and employs restricted maximum likelihood estimation to calculate parameter estimates.

Effects between the experimental and control group on continuous measures will be calculated with Cohen's *d*. Cohen's *d *is computed by subtracting the mean post-test score of the control group from the average score of the experimental group and dividing the difference by the pooled standard deviation. Effect sizes of 0.8 can be assumed to be large, while effect sizes of 0.5 are moderate, and effect sizes of 0.2 are small [35]. Estimated data from the LMM procedure will be used to analyse effect sizes.

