### Sample size

Power calculations are based on a moderate effect size of d=.50, comparing the PDSS-SR scores of the intervention group to the control group with a two-sided t-test (alpha .05, power 80%). To show this effect each group will consist of 64 participants [19], so the total sample size adds up to N = 128. Missing values will be imputed using regression imputation.

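### The only treatment effect the protocol defines is an unadjusted post-test difference; no stated analysis uses the baseline score or the two stratification factors, and the mixed model's terms are not given

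*Protocol article*

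**What the plan says.** All references are to the Methods of the protocol article.

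- **Sample size:** "Power calculations are based on a moderate effect size of d=.50", comparing PDSS-SR scores between the groups "with a two-sided t-test (alpha .05, power 80"%). From this "each group will consist of 64 participants", a total of 128.
- **Randomisation and procedure:** "Randomisation will be stratified for the presence or absence of agoraphobia symptoms (PDSS-SR item 4 score > 1) and the use of medication".
- **Instruments:** the outcome measures, including PDSS-SR and BAI, are taken at both t0 and t1.
- **Analyses, baseline data:** "Differences in demographic and baseline clinical characteristics will be computed with Chi-square tests", t-tests and ANOVA. This is the only use of baseline scores that the section states.
- **Analyses, model:** a linear mixed model fitted by REML is assigned to all analyses, with the purpose of dealing with missing values. No response vector, fixed effect or covariate is listed.
- **Analyses, effect:** Cohen's d is "computed by subtracting the mean post-test score of the control group from the average score of the experimental group", divided by the pooled SD. The section adds that model-estimated data will feed the effect sizes.

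**The concern.** The definition of d and the power calculation agree with each other: both describe a comparison of two groups of scores with no baseline or stratum term. That fits poorly with the rest of the design. The Discussion hypothesises greater improvement in the experimental arm, which is a statement relative to baseline. Randomisation is stratified on two factors that do not reappear under Analyses. Baseline scores are collected but are only to be tested for group differences. After proper randomisation such a test examines nothing but chance, and it gives no sound basis for choosing covariates.

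At stake is precision, not bias. An unadjusted post-test contrast carries whatever chance imbalance exists in baseline severity, and its residual variance includes a part that the baseline score could have removed. If stratification factors predict the outcome and are left out of the test, its standard error is somewhat too large. There is also a point about missing data. With two time points, a participant who lacks t1 adds information to a mixed model only if the t0 score is among the responses, and the article does not say that it is.

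**Working it through.** **Inputs from the protocol.** d = 0.50 (so SD = 1 on this scale), two-sided alpha 0.05, n = 64 per arm (Sample size). Entry range PDSS-SR 5-15 (Study population). Agoraphobia stratum defined by PDSS-SR item 4 (Randomisation and procedure), one of the seven items in the PDSS-SR total (Instruments).

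**Inputs assumed, because the protocol gives none.** Correlation r between baseline and t1 PDSS-SR: 0.3-0.5. Share of t1 variance explained by the two strata, R²: 5-15%.

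**1. The plan's own figure.** Non-centrality = d·√(n/2) = 0.50 × √32 = 2.83 on 126 df. Non-central t power is 80.1% at 64 per arm and 79.5% at 63. The stated 64 per arm reproduces.

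**2. Adjusting for baseline.** The residual SD falls by the factor √(1 − r²), so the non-centrality becomes 0.50·√32 / √(1 − r²), with one df lost (125).

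| Assumed r | SE relative to unadjusted | Non-centrality | Power at 64 per arm | n per arm for 80% |
|---|---|---|---|---|
| 0 (unadjusted) | 1.00 | 2.83 | 80.1% | 64 |
| 0.3 | 0.95 | 2.97 | 83.7% | 59 |
| 0.4 | 0.92 | 3.09 | 86.5% | 54 |
| 0.5 | 0.87 | 3.27 | 90.0% | 49 |

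The 5-15 entry range narrows the spread of baseline scores and may push r towards or below the lower end.

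**3. Leaving out the strata.** Stratified randomisation balances the factors across arms, so the true variance of the difference excludes the part they explain, while an unadjusted test still counts it. The reported SE is too large by 1/√(1 − R²), and the true two-sided alpha is 2·[1 − Φ(1.96/√(1 − R²))].

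- R² = 5%: SE ratio 1.026; critical value 1.96 × 1.026 = 2.01; alpha 4.4%.
- R² = 15%: SE ratio 1.085; critical value 1.96 × 1.085 = 2.13; alpha 3.4%.

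**4. The two gains overlap.** Correlations of 0.3-0.5 correspond to 9-25% of variance explained by baseline, against the 5-15% assumed for the strata. Because the agoraphobia stratum is derived from an item of the baseline total, part of what the strata explain is already in the baseline score. The gains must not be added.

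**5. Why the margin could matter.** The sample size contains no visible allowance for drop-out; the section says only "Missing values will be imputed using regression imputation". If 20% lacked t1 (assumed; 51 per arm observed), the same formulas give 70.6% power unadjusted, and 74.6%, 77.9% and 82.3% with baseline adjustment at r = 0.3, 0.4 and 0.5.

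**The case against.** The strongest reply is that the quoted sentence defines a descriptive effect size, not the inferential analysis. Inference is assigned to the mixed model, d is built from its estimates, and the model's terms are unlisted. Outcomes are measured twice, the hypothesis is about improvement, and the model is said to include incomplete cases; all three suggest that t0 may be modelled. A covariate list is also something a condensed article may leave to the full plan.

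Much of this stands. A reader might infer that the analysis ignores baseline and strata, and that its standard errors are therefore too wide. The document does not support that: it says neither that these variables enter the model nor that they are left out, and a formula for d has no standard error. A reader might also infer that the trial is underpowered. That is not so either: 64 per arm gives 80% power for the stated test with complete data, and sizing on an unadjusted test does not commit the analysis to one. Nor does anything say that the baseline tests will be used to choose covariates.

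What the reply does not remove is that the effect the article does define, and the basis on which it is powered, are both unadjusted. The bare absence of a covariate list would be no finding; the stated definition is a choice, and a better one is available from data already collected.

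**Conclusion.** The point holds as a free improvement. The stated effect is an unadjusted post-test difference, and no stated analysis brings in baseline PDSS-SR or the stratification factors. If the contrast is carried out as defined, the trial forgoes roughly 4 to 10 percentage points of power (80% against about 84-90%), conditional on r = 0.3-0.5. The loss from the strata is smaller over the ranges assumed, overlaps with the baseline gain, and errs in the conservative direction (alpha about 4.4-3.4% at R² of 5-15%). All these sizes rest on assumed values of r and R², and they vanish to the extent that the mixed model already contains these terms. There is no inflation of type I error, and the validity of the trial is not in question.

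**What to change.** Under Analyses:

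1. Define the primary contrast as the difference in PDSS-SR at t1 with a 95% CI, adjusted for baseline PDSS-SR, agoraphobia symptoms and medication use. Either ANCOVA on t1 or a mixed model with t0 and t1 as responses would serve. The latter lets participants who lack t1 contribute.
2. List the terms of the mixed model.
3. Compute Cohen's d from the adjusted difference, and say which SD divides it.
4. Report baseline characteristics by arm descriptively and drop the significance tests.

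The sample size can stay at 64 per arm as a conservative figure. The cost is wording only: every variable needed is already collected, and no recruitment, visit or questionnaire changes.
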